## Abstract

**Background:**

People with intellectual disabilities (ID) have low levels of physical activity (PA) together with accelerated aging profiles. Adherence to PA interventions for persons with ID is low based on barriers such as motivation. The IDEA study aims to determine the effect of two types of exercise programs, continuous aerobic (CAEP) vs sprint interval training (SIT), designed for seniors with ID on health-related physical fitness, cardiovascular parameters, quality of life (QoL), and emotional and cognitive function.

**Methods:**

In this trial, ninety seniors with ID between the ages of 40 and 75 yrs. from occupational health centers from the Autonomous Region of Catalonia (Spain) will be recruited. Participants will be randomly allocated to the CAEP, SIT, and control group. Both intervention groups will train 3 days/week, 1.5 h/day over 6 months. Outcome variables will be assessed at baseline, 6 months and 12 months. The outcome variables include weight, height, body composition, cardiorespiratory fitness, muscle strength, balance, flexibility, cardiovascular parameters (blood pressure, pulse-wave velocity, pulse-wave analysis), QoL and cognitive function. The intervention effect will be determined with mixed models with repeated measures to assess changes in the outcome variables over time (baseline to month 12) and between study arms. Relationship between variables will be analyzed with appropriate regression analyses.

**Discussion:**

Various studies reported on CAEP and SIT as exercise interventions for persons with ID with beneficial outcomes on body composition, fitness and blood pressure. To our knowledge, this is the first trial designed to analyse the positive changes on fitness, PA levels, cardiovascular, QoL and cognitive function promoted by CAEP training and SIT in seniors with ID. The findings of this study will assist in the development of more effective exercise interventions to ensure better compliance and adherence to exercise in seniors with ID.

**Trial registration:**

The trial is registered at the ISRCTN registry. Registration number: ISRCTN43594228. Registered 11 February 2019 – Retrospectively registered.

## Background

Persons with an intellectual disability (ID) present with alarming levels of sedentary lifestyles or very low levels of physical activity (PA) [1–3]. In addition, they present with greater multi-morbidity than persons without ID [4].

Although a direct relationship between health problems and low levels of PA or sedentary lifestyle has been established [5, 6], a large number of people do not meet the minimum levels of PA necessary for health benefits, especially older adults [7].

This relationship is of more concern in people with ID. The lack of support as well as multiple barriers faced by persons with ID to access sport facilities or exercise programs [8–10] put them in a vulnerable situation and at higher risk for suffering chronic diseases associated to sedentarism.

The aging process in people with ID starts around 40–50 years of age [11, 12]. Aging in adults with ID is associated with low physical fitness and health problems such as osteoporosis, diabetes, musculoskeletal disorders, dementia, hypertension and peripheral arterial disease [13, 14]. In Spain, adults with ID between 40 and 45 years old are considered older adults because the frequency of suffering these illnesses is similar to that of adults older than 65 years without ID [15].

Improved medical, healthcare and more person-centered care have gradually increased the mean life-expectancy of persons with ID [16]. Therefore, alternative and innovative solutions to maintain physical function and improve health and quality of life (QoL) of people with ID should include PA and exercise training.

To achieve clinically significant health-benefits and impact on health-related physical fitness, it is important to progress exercise volume and intensity [17]. Further, to maintain functional independence, cardiovascular health, muscle strength and prevent falls, resistance training should be included in multi-component exercise programs for people with ID [17–19]. Exercise programs for people with ID should take into account these general recommendations, without forgetting that delivering PA programs tailored to the specific needs of adults with ID is challenging because they need specific support, additional encouragement, and often, they may stop exercising if any discomfort is perceived [20].

Several exercise interventions for adolescents, young adults, middle-aged adults and seniors with ID implemented continuous aerobic exercise programs (CAEP), which is characterized by prolonged bouts of exercise at continuous steady-state intensity. Also, these interventions used CAEP combined with resistance, balance and flexibility [21–25]. They reported beneficial effects on peak oxygen consumption (VO_2_ peak), strength, balance and flexibility. Moreover, one study reported improvements in motor coordination and blood pressure [26]. In young adults, middle-age adults and seniors without ID, CAEP showed positive effects on improving brachial artery responses and central arterial stiffness [27, 28].

On the other hand, sprint interval training (SIT) is characterized by efforts performed at intensities ≥100% of the aerobic power and includes all-out or supramaximal short efforts (5–30-s) interspersed with active or passive recovery periods [29, 30]. Two studies conducted SIT programs in adolescents and young adults with ID [31] and adults with Down syndrome [32]. The authors reported improvements on VO_2_ peak, muscle endurance and blood pressure. In the general population, this exercise modality has been proposed as a time-efficient alternative strategy. Research studies reported that SIT elicited similar improvements in peripheral vascular structure and function [33], arterial stiffness [34], and VO_2_ peak than CAEP [35, 36]. Short bouts of all-out exercise may be an interesting time-efficient and more effective alternative to implement for training in seniors with ID who lack motivation for continuous exercises.

To the best of our knowledge, there is a lack of evidence in the literature documenting whether multi-component continuous or SIT exercise programs designed for seniors with ID will promote more significant benefits on health-related physical fitness, cardiovascular parameters, QoL, and emotional and cognitive function.

## Methods

### Study aims

The present trial aims to evaluate and compare the effectiveness of two different 6-months exercise programs on the health-related fitness of seniors with ID. Secondary to the main objective, this study will compare the effects of these interventions on the blood pressure, arterial stiffness, pulse wave velocity, PA levels and sedentary behaviors of the participants. Lastly, we seek to investigate the effect of the exercise programs on the QoL, emotional and cognitive function of the volunteers.

### Study design

The present study protocol describes a longitudinal three-armed parallel-group randomized controlled trial to evaluate and compare the effectiveness of two different multi-component exercise programs for seniors with ID.

A total of 90 participants from occupational day centers from Catalonia (Spain) will be recruited and randomly allocated to the CAEP, or SIT program or control group (CG). Participants from both exercise groups will receive a 24-week supervised exercise program, 3 times/week, 90 min/session. Participants from the CG will be visited by the researchers once a week to observe if they maintain their usual lifestyle. Outcome variables will be assessed at baseline (W − 1), month 6 (W 24; end of intervention) and month 12 (W 48; 6 months follow-up). After month 12, the CG will receive the SIT intervention in order to experience similar exercise-related health-benefits.

This study was approved by the Institutional Review Board (CER URL 2017_2018_008) and complies with the principles of the Declaration of Helsinki [37]. The trial is registered as a current randomized controlled trial (registration number: ISRCTN43594228; registration date: 11 February 2019). Figure 1 presents the participant flow for this trial. The present protocol follows the Standard Protocol Items Recommendations for Interventional Trials (SPIRIT) guidelines and fulfills the SPIRIT checklist.

**Fig. 1 Fig1:**
[figure not shown]
Proposed participant flow chart (CONSORT diagram). Abbreviation: W = week

### Setting and recruitment

Occupational day centers for adults and seniors with ID from the Autonomous Region of Catalonia (Spain) will be contacted to be part of the present study. For those centers interested in getting a more detailed description regarding the project, the research team will inform the relevant professionals at each center about the background and aims of the study.

Interested adults between the ages of 40 and 75 yrs. diagnosed with mild to moderate ID from the centers that volunteer to be part of the study, will be invited to the first meeting with their families/legal guardians and care-givers from the centers. During this meeting, the procedures of the trial, testing procedures, benefits, risks and the time required for the study will be explained. In addition, an information sheet about the research and an informed consent form for participants and parent(s)/legal guardian(s) will be distributed.

During the second visit and after the informed consent is signed, participants will be requested to bring a history of medical conditions. Participants will undergo a physical examination and complete a health screening questionnaire to disclose any pathology, contraindication and/or conditions that will preclude them from participating in exercise. Additionally, participants will complete a QoL questionnaire and the emotional and cognitive function assessments.

During the third visit, all volunteers will participate in familiarization sessions before baseline testing at the laboratory. The number of familiarization sessions will be repeated until the researcher observes that the participants are confident and able to perform all assessments correctly. Finally, during the fourth visit participants will complete the remaining assessments at the laboratory facilities. The same tests will be repeated at month 6 (end of training period) and month 12 (6 months follow-up).

Volunteers included in the present study and their parent(s)/legal guardian(s) will receive written feedback explaining the results and changes of the outcome variables at the end of the training period and at the end of the follow-up period. The participants will also be given a Polar M200 heart rate (HR) monitor (Polar Electro OY, Finland) to wear during the course of the study.

### Sample size

An average increase in VO_2_ peak of 0.2 L/min was reported in previous studies that implemented multi-component exercise programs for adults with ID [26, 32]. In the present study, a target increase of 0.2 L/min and a standard deviation of 0.1 L/min in VO_2_ peak has been used for sample size calculation [38]. Assuming a 95% confidence level, 5% alpha error, and 20% beta error, with a 1:1:1 ratio between groups, we will seek to recruit 24 participants per group. To allow for a drop-out rate of 20% throughout the study, a total of 90 participants, 30 participants in each group, will be required.

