## Discussion

To counteract the high prevalence of cardiovascular risk factors, decreased physical fitness [70–72], premature aging [11, 73], and overcome different barriers that seniors with ID have to face to live and active life [9, 74], it is essential to design exercise programs that best suit their needs. Therefore, the main objective of this study is to design two specific PA programs for seniors with ID and determine which of them will generate the greatest benefits in health-related physical fitness, cardiovascular parameters, QoL and emotional and cognitive aspects.

This study will span 12 months. After 6 months, participants will be followed up for 6 months without training. Finally, 12 months after starting the study, all participants in the CG will be offered the possibility to participate in the SIT program for 6 months.

Previously, numerous multi-component programs implemented continuous aerobic training in adolescents [22, 75], adults [24–26, 76, 77] and seniors with ID [21, 23, 78]. Also, some studies implemented SIT programs for adolescents and young adults with ID [31] and with Down syndrome [32]. Nevertheless, none of these studies implemented SIT programs specifically designed for seniors with ID. Furthermore, the present study will try to elucidate if exercise interventions promote beneficial changes on cardiovascular measures of central and peripheral arteries and which of these programs will have the most significant effect on the outcome variables.

Given the direct associations between cardiorespiratory fitness and mortality [79], muscular fitness and mortality [80], and the important effects of high intensity interval training programs on muscular adaptation and remodeling [81], it is necessary to further investigate the effects of SIT programs on overall fitness and vascular function in seniors with ID.

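### The sample size rests on a training gain of 0.2 L/min and names no contrast, so the stated 80% power is not established for CAEP versus SIT, and it does not follow from the stated inputs for any contrast

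*Protocol article*

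**What the plan says.** The Sample size section of the protocol article starts from prior evidence: "An average increase in VO_2_ peak of 0.2 L/min was reported in previous studies that implemented multi-component exercise programs for adults with ID". It then fixes the design values: "a target increase of 0.2 L/min and a standard deviation of 0.1 L/min in VO_2_ peak has been used for sample size calculation". The error rates are "Assuming a 95% confidence level, 5% alpha error, and 20% beta error", and the result is "with a 1:1:1 ratio between groups, we will seek to recruit 24 participants per group". Allowing for 20% drop-out gives 30 per group and 90 in total. The section does not say whether the calculation concerns each exercise arm against control, CAEP against SIT, or an overall three-group test.

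The objective is comparative. Under Study aims, the text reads: "The present trial aims to evaluate and compare the effectiveness of two different 6-months exercise programs on the health-related fitness of seniors with ID". The Discussion says that the main objective is to design two programmes and "determine which of them will generate the greatest benefits in health-related physical fitness". Study intervention states that warm-up, cool-down, resistance, balance and flexibility work are alike in the two exercise arms, that sessions are matched for total duration, and that the arms differ in the cycling modality. On the expected contrast, the Background reports that in the general population SIT "elicited similar improvements in peripheral vascular structure and function [33], arterial stiffness [34], and VO_2_ peak than CAEP". No CAEP–SIT difference in VO2 peak is stated anywhere. Statistical analysis specifies two-sided tests at 5% and effect sizes alongside significance tests.

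**The concern.** An average gain with training can serve as the difference between an exercise arm and control if controls do not change. It does not by itself give a difference between two programmes that share most of their content. The one stated effect size therefore does not address the question that the Discussion calls the main objective.

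A reader who sees 80% power beside an aim of finding the better programme will assume that the head-to-head test has that power. What a non-significant CAEP–SIT result could then support depends on a detectable difference and a precision that the protocol does not give.

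**Working it through.** **Inputs from the protocol article.** Difference 0.2 L/min, SD 0.1 L/min, two-sided alpha 5%, power 80%, 24 evaluable per arm, drop-out 20%.

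**1. Reproduce the plan's figure.** For two means, n per arm = 2 × (1.960 + 0.842)² × SD² / difference² = 2 × 7.849 × 0.01 / 0.04 = 3.92, so 4 per arm by the normal approximation. With the exact t test, 5 per arm gives 79% and 6 per arm gives 88%, so 6 are needed. With 24 per arm the power is over 99.9%. Other readings do not reach 24 either:

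| Reading of the calculation | n per arm |
|---|---|
| Bonferroni for three comparisons | 6–7 |
| Three-group ANOVA | 5–6 |
| SD of change = 0.1 × √2 = 0.141 | 8–9 |
| 99% power | 10–12 |

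Only the drop-out step reproduces: 24 / (1 − 0.2) = 30 per arm, 90 in total.

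**2. What would make 24 per arm correspond to 80% power.** By the exact t test, either the difference is about 0.083 L/min at SD 0.1, or the SD is about 0.24 L/min at a difference of 0.2. The protocol states neither value.

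**3. What 24 per arm delivers for CAEP versus SIT.** No difference is stated, so 0.05, 0.10 and 0.20 L/min are assumed as a range. The SD of 0.24 is also an assumption, taken from step 2. The test is a two-sample t test, two-sided 5%.

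| Assumed CAEP–SIT difference (L/min) | Power at SD 0.10 (stated) | Power at SD 0.24 (assumed) |
|---|---|---|
| 0.05 | 40% | 11% |
| 0.10 | 92% | 29% |
| 0.20 | >99.9% | 81% |

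**4. Precision.** The 95% CI half-width is t(46) × SD × √(2/24), with t(46) = 2.013 and √(2/24) = 0.2887.
- SD 0.10: 2.013 × 0.10 × 0.2887 = 0.058 L/min, which is 0.058 / 0.2 = 29% of the assumed training gain.
- SD 0.24: 2.013 × 0.24 × 0.2887 = 0.139 L/min, which is 70% of it.

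These figures come from a simple two-group comparison at one time point. A mixed model with baseline in it could be somewhat more precise, and a multiplicity adjustment would lower the power.

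**The case against.** The strongest reply is that the trial is not shown to be too small. At the protocol's own SD, 24 per arm has 92% power for half the assumed training gain. The poor figures need an SD of 0.24, which the protocol never states. This stands: a reader might infer that the head-to-head comparison is underpowered, but the document does not establish that. Adequacy turns on an SD and a CAEP–SIT difference that it does not justify.

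Second, Study aims covers evaluating as well as comparing the programmes, and there is a control arm, so 0.2 L/min may have been meant for exercise against control. This also stands, but it does not rescue the 80%, which fails at the stated inputs for that contrast as well.

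Third, the statement about similar gains concerns the general population. The same Background section suggests that short all-out bouts may be more effective for seniors with ID, and says that evidence on which programme brings more benefit is lacking. The statement therefore cannot be read as the authors' expectation of no difference here. Nor does a gap of 0.2 L/min require one programme to do nothing or the other to double its gain: gains of 0.1 and 0.3 would also produce it.

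Fourth, a reader might fault the absence of an equivalence or non-inferiority margin. The question posed is which programme is better, tested two-sided, and a superiority question needs no margin. The protocol nowhere proposes to read a null result as equivalence.

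None of these replies supplies a named contrast or a CAEP–SIT difference.

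**Conclusion.** The point holds as a mismatch within the protocol. The only effect size is a gain from training, no powered contrast is named, and a main objective is a comparison for which no difference is stated. The 80% power is therefore not established for CAEP versus SIT. It is not established for exercise against control either, because the stated inputs call for about 6 per arm, not 24.

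The consequence for the head-to-head comparison depends on the SD. At the stated 0.1, differences of about 0.083 L/min or more are detectable with 80% power. At an assumed 0.24, that power is reached only near 0.2 L/min. The true SD and the CAEP–SIT difference of interest remain unknown from the document.

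**What to change.** 1. In Sample size, name the contrast or contrasts that the calculation covers, and restate the power from a justified SD for the measure analysed. Do not attach the present 80% to exercise against control; it is not correct there at the stated inputs.
2. State separately what 24 per arm delivers for CAEP versus SIT: the detectable difference, the power over a range of differences labelled as assumptions, and the expected CI half-width, at the stated SD and at a larger one.
3. Commit to reporting CAEP minus SIT in VO2 peak at week 24 as an estimate with a 95% CI, and state that a non-significant test will not be taken to show that the programmes are similar.
4. In the Discussion, replace the promise to find the more beneficial programme with an aim of estimating the difference between them.

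The cost is a change of wording and a less favourable stated claim for the head-to-head comparison. No additional participants are required.

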### Statistical analysis

Outcome analysis will be performed blinded to group allocation. The descriptive analysis of the sample will be expressed as mean and standard deviation for continuous and normally distributed variables, meanwhile non-normal distributed variables will be presented as median and interquartile range. Categorical variables will be presented as number and percentage with their standard error. Normality and homogeneity will be tested by using Kolmogorov-Smirnov test and Levene’s test, respectively. When necessary, appropriate transformations will be applied in case of non-normal distributions.

The analysis of the data set will follow an intention-to-treat design and all randomized participants for whom baseline assessments were conducted will be included in the final analysis.

To analyze the outcomes of the study we will use linear mixed-effect models with repeated measures. We will assess changes over time (W -1; W 24; W 48) and between study arms. Appropriate post-hoc tests will be implemented to analyze within and between group differences of the study arms at each time point. Categorical variables will be analyzed using Pearson’s χ-squared or Fisher’s exact test at baseline, after intervention and follow-up period.

To examine the correlations between the different outcomes, Pearson’s correlations and multiple regression analysis will be performed.

If necessary, baseline differences between the trial arms on outcomes variables will be used as covariates and fitted as factors in the models.

Two-sided tests of statistical significance will be used in all analyses. Effects size of the interventions will be presented in addition to significance tests. Significance levels will be set at an alpha level less than 5%. Statistical analyses will be conducted using SPSS v. 25 (IBM SPSS Statistics, Chicago, IL, USA).

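### The 24 per group cannot be reproduced from the printed sample-size inputs, which need about 6 per group for 80% power

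*Protocol article*

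**What the plan says.** The Sample size section takes its effect from earlier exercise programmes in adults with intellectual disability: "An average increase in VO_2_ peak of 0.2 L/min was reported in previous studies". It then says that "a target increase of 0.2 L/min and a standard deviation of 0.1 L/min in VO_2_ peak has been used for sample size calculation". It does not say whether 0.1 is the SD of the change or of a single measurement, or which comparison the 0.2 refers to (within an arm, exercise against control, or one programme against the other).

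The error rates are given as "Assuming a 95% confidence level, 5% alpha error, and 20% beta error". The result follows: "with a 1:1:1 ratio between groups, we will seek to recruit 24 participants per group". The last step is the drop-out allowance: "To allow for a drop-out rate of 20% throughout the study, a total of 90 participants, 30 participants in each group, will be required".

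The Statistical analysis section fixes the sidedness: "Two-sided tests of statistical significance will be used in all analyses". VO2 peak, from the cardiopulmonary exercise test, is the primary outcome.

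**The concern.** A target of 0.2 L/min against an SD of 0.1 L/min is a difference of two standard deviations. That is a very large effect, and very few participants are needed to detect it. Twenty-four per group is what one expects for an effect of a little over 0.8 standard deviations. The printed number is about four times what the printed inputs call for.

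This paragraph is the article's only quantitative justification for the size of the trial. A reader needs it to know what between-arm difference in VO2 peak the trial was built to detect, particularly because the trial also aims to compare two active programmes. As printed, the smallest difference detectable with 80% power could be about 0.083 L/min or 0.20 L/min, depending on which element is taken at face value.

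**Working it through.** **Inputs.** Δ = 0.2 L/min, σ = 0.1 L/min, α = 0.05, β = 0.20 and allocation 1:1:1 come from Sample size; two-sided testing comes from Statistical analysis. Standardised difference d = 0.2/0.1 = 2.0.

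**Drop-out step.** 24/(1 − 0.20) = 30 per group, and 3 × 30 = 90. This reproduces.

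**Normal approximation.** n = 2(z₀.₉₇₅ + z₀.₈₀)²σ²/Δ² = 2 × (1.960 + 0.842)² × (0.1/0.2)² = 2 × 7.85 × 0.25 = 3.9, so 4 per group.

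**Exact two-sample t-test.** The noncentrality is d√(n/2) on 2n − 2 degrees of freedom.
- n = 5: noncentrality 3.16, power 79.1%.
- n = 6: noncentrality 3.46, power 87.6%.

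So 6 per group.

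**Other readings of the printed inputs, all at 80% power.** If 0.1 is the SD of a single measurement, the SD of the change is 0.1 × √(2(1 − ρ)). Among non-negative correlations with baseline this is largest at ρ = 0, where it equals 0.141. The last column uses that least favourable value.

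| Test | n per group, 0.1 as SD of the analysed quantity | n per group, 0.1 as raw-score SD, ρ = 0 |
|---|---|---|
| Two-sample t, two-sided 5% | 6 | 9 |
| Two-sample t, Bonferroni for 3 pairs | 7 | 13 |
| Three-arm ANOVA, means 0, 0.2, 0.2 | 5 | 9 |
| Three-arm ANOVA, means 0, 0.1, 0.2 | 6 | 11 |
| Paired t within one arm | 5 | not run |

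Going outside the stated alpha does not close the gap either. A two-sided alpha of 0.01 with the raw-score reading gives 14 per group, and raising power to 95% as well gives 20.

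**Power of 24 per group with the printed inputs.** Noncentrality 2.0 × √12 = 6.93 on 46 degrees of freedom gives power 0.999999. With Bonferroni for three pairs it is 0.99999.

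**Working back from 24.** For 80% power with 24 per group in one two-sided 5% t-test, d = 0.826. That means:
- σ = 0.2/0.826 = 0.242 L/min if Δ = 0.2; or
- Δ = 0.826 × 0.1 = 0.083 L/min if σ = 0.1.

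The normal approximation gives 0.247 and 0.081. These figures show the size of the gap. They are not estimates of what was actually used.

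**For scale.** Six per group with 20% drop-out is 6/0.8 = 7.5, so 8 per group and 24 in total. That this total equals the printed per-group figure is no evidence of how 24 arose, because the article gives 24 per group and before drop-out.

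**The case against.** The strongest reply is that something was left out of a condensed article rather than misprinted. The 0.2 L/min is an average increase from earlier programmes, and the authors may have planned for a smaller difference between the two active arms. Taking Δ = 0.1, σ = 0.1 and Bonferroni for three pairs, as an assumption only, gives 23 per group by the t-test (21 by the normal approximation), which is close to 24. Training takes place in groups of 10, so an unstated design effect is also conceivable. Going from 6 to 24 needs 1 + 9 × ICC = 4, an ICC of about 0.33. The calculation also cites a reference that is not available here.

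This stands in part. A reader might infer that one of the printed inputs must be wrong, but the document does not support that: an omitted comparison or adjustment would explain the gap as well. It does not rescue the paragraph, however. The article says that 0.2 and 0.1 were the values used, names no other allowance than drop-out, and prints a number that they do not give. That is a stated figure that fails to follow, not a detail left to a fuller document.

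The second reply is that the discrepancy is harmless because the trial is larger than its inputs require. It is right that those inputs do not show an underpowered trial, and that no analysis or conduct step depends on the figure. But the reassurance rests on the SD of 0.1 being true, and the conflict is what puts that in doubt.

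**Conclusion.** The 24 per group does not follow from the printed inputs. They need about 6 per group (5 to 7 across the usual tests), or 9 to 13 if 0.1 is a raw-score SD uncorrelated with baseline. The printed number is therefore about 4 times the requirement on the direct reading (24/6), and still about 1.8 times at the least favourable of these readings (24/13). The inputs, the 80% power and the 24 cannot all be right as they stand, and the document does not show which is wrong or whether an adjustment is missing.

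Two stronger conclusions are tempting and should not be drawn. One is that 80% is not the design's power: it could be the true power if, for instance, the SD were about 0.24 L/min, so the real power is simply unknown from the text. The other is that a null result or a confidence interval could not be interpreted: the interval will come from the observed SD and sample size, and can be read against 0.2 L/min whatever was planned.

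The result assumes two-sided 5% testing and 80% power, as stated, and a comparison of means in independent participants. The drop-out step is not in error.

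**What to change.** Keep 90 participants. Correct the Sample size paragraph by stating what actually produced 24: the comparison (which arms, and whether change or end value), the test, whether the SD is of change or of a single measurement and where it comes from, and any allowance for multiplicity, clustering or correlation.

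If 0.2 and 0.1 L/min truly were the inputs, replace the power statement: 24 evaluable participants per group give over 99.99% power for 0.2 L/min, or 80% power for a difference between two arms of about 0.083 L/min (single two-sided 5% t-test).

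The SD should not be chosen by working back from 24. The 0.24 L/min above shows the size of the mismatch and is not a value to adopt without a source.

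The cost is one or two sentences, with no change to recruitment, analysis or conduct.
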